## Background

The morbidity and health care costs associated with decompensated cirrhosis are substantial because patients require complex medical care to manage debilitating complications of their disease [1, 2]. People with decompensated cirrhosis are often prescribed multiple medications for therapeutic or prophylactic use to reduce the negative health effects of cirrhosis. However, many patients lack the knowledge and skills required to contribute effectively to disease management [3, 4].

On average, this patient group has approximately three hospital admissions each year [1, 5], reflecting the high burden of illness and use of health care resources. The number of medications prescribed on hospital discharge has been found to predict rehospitalization rate and time to first hospital readmission, independently of serum biomarkers that also predict poor outcomes [2]. With recurrent admissions, more medicines are prescribed and/or the medication regimen is altered. This increases opportunities for miscommunication and nonadherence, thereby increasing the risk of medication errors and rehospitalization.

Poor knowledge of cirrhosis, medications, self-monitoring, and important dietary and lifestyle modifications has been described in ambulatory Australian patients with cirrhosis [4]. Low medication adherence was identified in over one-fourth of patients (27.5%), and discrepancies among conventional medications were also seen in 54.0% of patients with cirrhosis attending general hepatology clinics [6]. Communication barriers between patients and clinicians are a recognized impediment to patient care that may result in clinically significant discrepancies and other medication-related problems (MRPs) [7]. MRPs are events or circumstances involving medications that actually or potentially interfere with an optimum outcome of care [8]. They are complex and multifaceted issues that may be the result of numerous interacting factors. Examples of MRPs that may occur in patients with decompensated cirrhosis are presented in Table 1. It has been estimated that up to 22% of 30-day readmissions among patients with decompensated cirrhosis may be preventable with improved medication management or more frequent monitoring [2].

**Table 1 Tab1:** Potential medication-related problems in patients with decompensated cirrhosis

Classification and definition	Subtype	Example
Adverse drug reaction		

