**Fig. 1 Fig1:**
[figure not shown]
Standard Protocol Items: Recommendations for Interventional Trials (SPIRIT) flow diagram of participant recruitment and study navigation. *MRP* Medication-related problem

All participants will complete a baseline survey prior to their scheduled outpatient clinic review. Validated questionnaire tools will be used to determine baseline medication adherence, medication beliefs, illness perceptions, and QoL, in addition to patient knowledge of important dietary and lifestyle modifications. The survey will be completed with a study coordinator over the telephone or in person in a private clinic room, or it will be self-completed by the participant in the clinic waiting room. Patient carers or family members will be involved if necessary.

Usual care participants will subsequently receive routine review and education by their hepatologist according to the current model of care in the hepatology clinic. Intervention participants will be reviewed by a clinical pharmacist to receive the education and medication management intervention (described below) in addition to routine review and education by their hepatologist. Intervention participants will also receive three further educational contacts from the clinical pharmacist in addition to scheduled routine hepatologist review within the following 6-month period.

All participants will be resurveyed at follow-up (*t*
_3_, approximately 6 months post-enrollment) to explore changes in their medication adherence, medication beliefs, illness perceptions, QoL, and knowledge. Patient outcome data will be collected at 52 weeks (*see* “Study endpoints and data collection” section below).

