### Data analysis

Data will be coded and stored in a password-protected database and analyzed using a statistical software package (IBM SPSS Statistics version 20.0; IBM, Armonk, NY, USA). Study endpoints experienced for each treatment group will be formally analyzed on an intention-to-treat basis [36]. Important potential confounders will be included in a secondary multivariate analysis (e.g., hospital admission, mortality). Post hoc subgroup analysis will be used to further explore outcomes according to the intensity of the intervention and completeness of relevant personalized education received by intervention participants.

The study endpoints will be presented quantitatively (proportions, statistical differences between groups) and qualitatively (description of discrepancies, MRPs, and some patient-reported medication beliefs and illness perceptions). All tests will be two-tailed, and significance will be set at α = 0.05. Continuous and normally-distributed variables will be presented as mean ± SD. Differences between groups will be analyzed using one-way analysis of variance. Non-normally distributed data will be presented as median (range), and nonparametric tests will be used to analyze differences between groups. Categorical data will be analyzed using Pearson’s chi-square test or Fisher’s exact test. Pearson’s correlation or Spearman’s rank correlation coefficient will be used to identify linear relationships between normally distributed and non-normally distributed continuous variables, respectively.

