Differences in the study endpoints of interest will be examined between the intervention and control groups at baseline and at follow-up. The endpoints will be examined at baseline to test for homogeneity between groups (effectiveness of randomization) and to identify clinical variables that may influence endpoints (e.g., Model for End-Stage Liver Disease score; Child-Turcotte-Pugh classification; decompensation history, including event date, type, severity, and recurrence; hospitalization frequency; age; sex; biochemical abnormalities; and other prognostic variables). Clinically significant differences at baseline between groups will be adjusted for during the final analysis. Changes in the frequency of medication discrepancies, self-reported adherence, QoL, medication beliefs, illness perceptions, and patient knowledge at follow-up will be examined to measure the effect of the intervention on study outcomes at group and individual levels. The primary endpoint of medication discrepancies will be explored using total frequency of instances and frequency of instances per patient and per medication group. Comparison between intervention and control groups at baseline and *t*
_3_ will be made using total number of instances per group, total number of high/very high risk instances per group, mean/median number of instances per patient, and mean/median number of high/very high risk instances per patient.

Predictors of clinical outcomes will be identified using binary logistic regression to determine the OR (95% CI). A multivariable logistic regression model will be used to determine independent predictors for patient outcomes. The multivariable logistic regression model will be constructed using variables of clinical significance (severity of disease; decompensation history, including date, type, severity, and frequency of events; other prognostic variables) and statistical significance as determined by univariate analysis.

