Time to first episode of decompensation and time to death (cause-specific and all-cause) will be assessed using Kaplan-Meier survival curves. The curves will be compared with the log-rank test statistic. Cox proportional hazards modeling will be used to calculate HRs, after testing the proportional hazards assumption. Patients will contribute person-time from the date of recruitment until the earliest of end of follow-up (12 months) or death (date of death to be obtained from medical records). Competing risks analysis will be performed in which we encode, as separate events, time to first readmission with a cirrhosis-related episode, death resulting from cirrhosis, or death resulting from other causes. This will be extended to multivariate analysis if there are a sufficient number of events.

It is anticipated that a proportion of participants (approximately 30%) will be lost from the study before completing follow-up assessments at *t*
_3_. Although the sample size calculation has been adjusted to accommodate for this loss, subjects who have completed only one assessment will be included in the analyses to establish baseline parameters in both treatment groups. With respect to changes from baseline, data imputation will be considered. In decompensated cirrhosis, dropouts due to death are informatively censored, and thus the responses of patients with missing data will be modeled explicitly. Subjects will be matched using baseline demographic and patient-reported outcomes, repeating this technique for both intervention arms. Imputation methods such as a hot-deck imputation and iterative regression imputation will be used. The sensitivity of the results to each of these methods will be assessed to quantify the degree of bias present.

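### Predictors of patient outcomes are assigned to logistic regression, but admissions are collected as a count and no count or rate model is named for them

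*Protocol article*

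**What the plan says.** Two sentences of the Data analysis section fix the method for predictors: "Predictors of clinical outcomes will be identified using binary logistic regression to determine the OR (95% CI"), and "A multivariable logistic regression model will be used to determine independent predictors for patient outcomes". Neither says which outcomes are meant or how an outcome that is not binary becomes binary.

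Other sections show what the outcomes are. Study navigation states: "Patient outcome data will be collected at 52 weeks". Table 3 lists only hospitalization and survival at t4, which I read as the 52-week point. The section on hospitalization and mortality collects the number of admissions, their frequency and their duration. The Background gives a rate: "On average, this patient group has approximately three hospital admissions each year".

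The Data analysis section names three other methods that touch these outcomes:

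- a secondary adjusted analysis: "Important potential confounders will be included in a secondary multivariate analysis (e.g., hospital admission, mortality"), with no model form given;
- Kaplan-Meier curves for first decompensation and death, followed by Cox models: "Cox proportional hazards modeling will be used to calculate HRs, after testing the proportional hazards assumption";
- "Competing risks analysis will be performed in which we encode, as separate events, time to first readmission with a cirrhosis-related episode", with the two types of death as the other events; "This will be extended to multivariate analysis if there are a sufficient number of events".

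No count or rate regression is named anywhere in the protocol.

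**The concern.** A binary model cannot take a number of admissions as its outcome. An analyst who follows the text must first choose a cut, and the protocol gives none, so the choice could be made after the data are seen. Any cut treats a patient with two admissions and one with eight as alike if both fall on the same side.

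Time at risk is also lost. The sample size section predicts 6-month mortality of 10% to 15%. Patients who die early have less opportunity to be admitted, so a strong predictor of death can look protective against admission. The protocol defines person-time to 12 months or death for its survival analyses, but the logistic model as described does not use it.

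At stake is whether about 106 patients can show which characteristics go with a heavy admission burden. Real predictors could be missed, and some could be distorted by deaths.

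**Working it through.** **The plan's own figure.** The protocol gives no power for the predictor analysis. Its only sample size figure is for the primary endpoint and it reproduces: 2 × (1.96 + 0.842)² × (2.5/1.56)² = 2 × 7.85 × 2.568 = 40.3, so 41 per arm. I take only the total of 106 from that section.

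**Inputs.** From the protocol: N = 106, two-sided α = 0.05, about 3 admissions a year. Assumed, because the protocol is silent: a binary predictor that splits patients 53/53, rate ratio 0.5, negative binomial counts with variance m + m²/k and k = 0.5, 1 or 2, and a lower mean of 1 as a sensitivity case. The higher-rate group has mean m₁ = 3 (or 1) and the other m₂ = m₁/2. Everyone is followed for 12 months in this first step.

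**Formulas.**

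- Count model: SE of the log rate ratio = √[(1/m₁ + 1/k)/53 + (1/m₂ + 1/k)/53]; power = Φ(ln 2/SE − 1.96).
- Any/none: p = 1 − (k/(k + m))^k; power = Φ{[|p₁ − p₂|√53 − 1.96√(2p̄(1 − p̄))]/√[p₁(1 − p₁) + p₂(1 − p₂)]}.

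**One case in full (m₁ = 3, m₂ = 1.5, k = 1).** SE = √[(1.333 + 1.667)/53] = 0.238; 0.693/0.238 − 1.96 = 0.95; power 83%. For any/none, p₁ = 0.75, p₂ = 0.60 and p̄ = 0.675; (1.092 − 1.298)/0.654 = −0.32; power 38%.

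| m₁, m₂ | k | Any admission | Count model | Any/none | Loss (points) |
|---|---|---|---|---|---|
| 3, 1.5 | 0.5 | 62% vs 50% | 62% | 24% | 38 |
| 3, 1.5 | 1 | 75% vs 60% | 83% | 38% | 45 |
| 3, 1.5 | 2 | 84% vs 67% | 95% | 52% | 43 |
| 1, 0.5 | 0.5 | 42% vs 29% | 48% | 28% | 20 |
| 1, 0.5 | 1 | 50% vs 33% | 62% | 41% | 21 |
| 1, 0.5 | 2 | 56% vs 36% | 71% | 53% | 19 |

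**With deaths.** At constant hazard (an assumption), 10% to 15% mortality by 6 months is 1 − 0.90² = 19% to 1 − 0.85² = 28% by 12 months. A simulation with deaths, and with log person-time as offset in the count model, gave any/none 23–48% against 60–95% at a mean of 3 (losses 60 − 23 = 37 to 95 − 48 = 47). At a mean of 1 it gave 26–51% against 41–67% (losses 41 − 26 = 15 to 67 − 51 = 16).

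**Sensitivity.** If 3 is the average over both groups (means 4 and 2), the formulas give 64% vs 22%, 86% vs 34% and 97% vs 46% for k = 0.5, 1 and 2, so losses of 42 to 52 points. With the same average and a weaker contrast (rate ratio 1.5, equivalently 0.67), they give 28% vs 10%, 44% vs 15% and 62% vs 19%, so losses of 17 to 43 points.

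**The case against.** The best defence is that the two sentences never say that admissions will be a logistic outcome. Death by cause, a new decompensation event and low adherence are binary or easily made so, and logistic regression is acceptable for them. This is also an exploratory analysis in a condensed article, and the exact outcome of each model may sit in an analysis plan that is not shown. That lowers the weight of the point. It does not remove it: the protocol states the method for patient outcomes in general, one of the two outcomes collected at t4 is hospitalization, and no alternative is named for its count.

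Four stronger readings are tempting and should not be drawn.

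- A reader might infer that logistic regression is the only predictor method. It is not. Cox and competing-risks models are planned, and they respect follow-up time for death, first decompensation and first cirrhosis-related readmission. They leave out repeat admissions, and the multivariable extension depends on the number of events.
- A reader might infer that admissions will be cut at any versus none. The protocol sets no cut. Any/none is used above as the natural illustration.
- A reader might infer a fixed loss, such as half the power, or that nearly every patient will be admitted. Neither follows. Three a year is a literature figure. Eligible patients are outpatients whose last complication may lie up to two years back, and those under transplant or palliative teams are excluded. With k from 0.5 to 2 and a mean of 3, 62% to 84% have any admission. This is why a mean of 1 is included.
- A reader might infer that the hypothesis of fewer admissions in the intervention arm (H7) is compromised. The quoted sentences concern predictors. For differences between arms the protocol plans nonparametric tests on non-normal data, which can use the whole count.

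Those tests and the planned rank correlations could also relate the count to single predictors, but they neither adjust for other variables nor account for time at risk.

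**Conclusion.** The point holds in limited form. The stated predictor method does not fit the number of admissions without an undefined dichotomisation and a disregard of time at risk, and the time-to-event models do not fill that gap. With 106 patients, an evenly split predictor, a rate ratio of 0.5, a mean of 1 to 3 a year and k of 0.5 to 2, an any/none analysis loses roughly 15 to 45 points of power. The direction is the same in every setting examined. The size is not derivable from the protocol, which gives no predictor, effect or dispersion. The matter is minor: it concerns a secondary, exploratory analysis and leaves the primary comparison of medication discrepancies untouched.

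**What to change.** Replace the two general sentences with a statement by outcome:

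- Number of admissions, liver-related and all: negative binomial regression with log person-time to 12 months or death as offset, reported as rate ratios with 95% confidence intervals.
- Death: the Cox model already planned, used as the predictor model.
- Outcomes that are binary by nature: logistic regression, with each outcome named.

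Admission numbers and dates of death are already to be taken from medical records, so no new data are needed. The cost is a change of wording and a small amount of analysis work.

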### Participant recruitment

The Hepatology Outpatient Centre’s appointment database will be prescreened for eligible participants who are scheduled for routine review by a hepatologist. Persons identified as eligible will be contacted via telephone in the week preceding their appointment to discuss the study and offer participation. Participants will be given instructions to arrive 15 minutes early for their appointment, bring all medications to the clinic, and ask their carer or responsible family member to accompany them if appropriate. Consented participants will be randomly allocated to one of the two study arms: (1) intervention or (2) usual care.

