### Power calculation and sample size determination

On the basis of a primary endpoint of a 50% reduction in medication discrepancies (3.12 ± 2.5 per patient [6] to 1.56 per patient), 41 participants will be required per treatment arm to achieve ≥80% statistical power. Median survival in decompensated cirrhosis is 2 years [37]. Therefore, a 6-month mortality rate between 10% and 15% among the study cohort is predicted. The Hepatology Outpatient Centre’s attendance failure/reschedule rate is approximately 20%. Therefore, a possible 30% loss will be accounted for, and at least 106 participants will be recruited.

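### Univariate significance is one of two entry criteria for the multivariable logistic model, so predictors kept on their p-value will often be false or have exaggerated odds ratios

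*Protocol article*

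**What the plan says.** The Data analysis section of the protocol article first reports odds ratios with 95% confidence intervals from binary logistic regression. It then states: "A multivariable logistic regression model will be used to determine independent predictors for patient outcomes". Two kinds of variable enter that model. The first is "variables of clinical significance (severity of disease; decompensation history, including date, type, severity, and frequency of events; other prognostic variables". The second is those with "statistical significance as determined by univariate analysis". The text does not say whether a variable must meet both criteria or only one, and it names no single outcome or time point.

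The only significance level given is general: "All tests will be two-tailed, and significance will be set at α = 0.05". No separate threshold for screening is stated.

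The same section makes the multivariate extension of the competing-risks analysis depend on having enough events. The logistic model carries no such condition. Time to death is separately assigned to Kaplan-Meier curves, the log-rank test and Cox models over 12 months.

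**The concern.** The rule lets the outcome data choose the covariates and then reports the refitted model as if the covariates had been fixed in advance. A variable that passes by chance is carried forward with an estimate that is too large. One with a real but modest effect tends to pass only when its estimate is by luck high. The printed interval takes no account of either.

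The candidate list is long for the size of the trial. The logistic sentence names disease severity and four aspects of decompensation history, and adds an open class of other prognostic factors. Earlier in the section, in the paragraph on baseline variables that may influence endpoints, ten items are named: MELD, Child-Turcotte-Pugh, decompensation date, type, severity and recurrence, admission frequency, age, sex and biochemistry. That list is also left open.

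At stake is whether the variables reported as independent predictors can be believed, and whether their odds ratios can be used in later work.

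**Working it through.** **Number of patients.** The plan's sample size reproduces. From "3.12 ± 2.5 per patient [6] to 1.56 per patient", the difference is 1.56 with SD 2.5. With two-sided α = 0.05 and 80% power, n per arm = 2 × (1.960 + 0.842)² × 2.5² / 1.56² = 40.3, rounded up to 41. This agrees with "41 participants will be required per treatment arm to achieve ≥80% statistical power". The stated minimum of 106 agrees with 82 × 1.3 = 106.6.

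**Number of deaths.** The article gives no count, so these are derived under constant hazard.
- From "Median survival in decompensated cirrhosis is 2 years": 12-month mortality = 1 − 0.5^(12/24) = 29.3%, and 106 × 0.293 = 31.0 deaths.
- From the stated 6-month mortality of 10% to 15%: 12-month mortality = 1 − 0.90² = 19.0% to 1 − 0.85² = 27.75%, or 20.1 to 29.4 deaths.
- The 12-month range is therefore about 20 to 31 deaths. With 10 candidates that is 2.0 to 3.1 deaths per candidate; with 15 it is 1.3 to 2.1.
- At 3 years: 1 − 0.5^(36/24) = 64.6%, or about 69 deaths and 37 survivors.

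**Chance that a null variable passes.** With k independent null candidates screened at 0.05 (assumed, since no screening level is given), P(at least one passes) = 1 − 0.95^k. This is 40% for k = 10 and 54% for k = 15. It does not depend on the number of events.

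**Simulation of screening and refitting.** There are 106 patients, an event rate of 29.3% (about 31 events) except in the last row, two true predictors with the stated odds ratio (OR) per SD, and the remaining candidates pure noise. Every candidate is screened at p < 0.05 and those that pass are refitted together, with 1,500 trials per row. The number of candidates, the ORs and the correlation are assumptions. The sixth column fits all candidates with no screening.

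| Candidates, true OR, correlation | Noise variable enters | Noise variable significant in final model | Median OR, selected true predictors | Coverage, all selected | Median OR, no screening |
|---|---|---|---|---|---|
| 10, 1.50, 0 | 33% | 27% | 1.85 | 72% | 1.59 |
| 10, 1.50, 0.3 | 64% | 14% | 1.62 | 93% | 1.60 |
| 15, 1.50, 0 | 46% | 38% | 1.84 | 64% | 1.63 |
| 15, 1.50, 0.3 | 76% | 18% | 1.56 | 94% | 1.63 |
| 10, 2.00, 0 | 31% | 22% | 2.18 | 87% | 2.21 |
| 10, 1.25, 0 | 30% | 29% | 1.76 | not run | 1.29 |
| 10, 1.50, 0, about 13 events | 30% | 26% | 2.22 | not run | 1.65 |

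The formula agrees with the first row: eight null candidates give 1 − 0.95^8 = 34%, against 33% simulated.

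Three things follow.
- False predictors appear in every setting. A noise variable is significant in the final model in 14% to 38% of trials.
- Exaggeration caused by selection is marked when candidates are uncorrelated and effects are modest. At correlation 0.3, or with a true OR of 2.00, the selected ORs are no more inflated than those from fitting all candidates.
- Coverage over all selected predictors runs from 64% to 94%. For selected true predictors alone it is 84% to 98%. The unscreened model covers at 93% to 95%.

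**The case against.** Several stronger readings are tempting, and the document does not support them.

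- A reader might infer that the p-value alone decides entry. It does not, because clinical significance is the other criterion. If either criterion suffices, severity and decompensation history enter unscreened, and the harm falls on variables admitted only by their p-value. If both are required, the p-value decides among the clinical candidates. The simulation screens every candidate, so it matches the second reading best.
- A reader might infer that the whole analysis rests on about 31 deaths. That figure is derived, is the top of a 20 to 31 range, and applies only to death by 12 months. The model is for patient outcomes in general. The Background cites about three admissions per patient per year, so admission outcomes should supply more events. Death already has a planned Cox model.
- A reader might infer that the intervals will always be too narrow. At correlation 0.3 coverage is 93% to 94%, and overlapping measures such as the two severity scores are likely to be correlated. Very low coverage among selected variables when nothing is real is almost built in, because a null variable passes when its own univariate interval excludes the truth.
- A reader might infer that the article offers these prognostic predictors as guidance for care. Its statement about future management concerns modifiable factors in medication management.

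It can also be said that the final covariate list belongs in a statistical analysis plan that is not shown. That is fair for the list itself. It does not excuse the entry rule, which the article states. More events would reduce the exaggeration, but each independent null variable would still pass 5% of the time.

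**Conclusion.** The point stands as a minor improvement to a secondary analysis. Univariate significance on the same data is a stated entry criterion, with no correction, penalisation or event condition attached. Predictors retained through it will often be false or exaggerated, and their intervals ignore the selection and may undercover, depending on correlation and effect size.

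These sizes rest on assumptions: screening at 0.05, ten or more candidates, about 106 patients and, for deaths, constant hazard. The problem is sharpest for death by 12 months. It is milder for more frequent outcomes, provided the group without the event is not itself small; for 3-year death the smaller group would be the roughly 37 survivors.

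Nothing here touches the primary comparison of medication discrepancies or the planned survival comparison between arms.

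**What to change.** Remove univariate significance as an entry criterion. Before outcome data are examined, write down for each logistic outcome a short covariate list chosen on clinical grounds (for example, one severity score, prior decompensation, prior admissions and age). Size it to the expected events, or to the non-events if those are fewer. Fit that model once, use penalised estimation if events are few, and label the results exploratory. For death, rely on the Cox model already planned.

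The list needs to be short as well as prespecified. In the simulation, fitting 10 or 15 unscreened candidates restored coverage but still gave a median OR of 1.59 to 1.63 for a true 1.50 with about 31 events.

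The change is to analysis wording only and needs no extra patients or data. Its downside is that fewer candidate predictors are examined.

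### Kaplan-Meier for time to first decompensation in effect censors deaths, so it overstates the proportion affected, and the planned competing-risks analysis does not name this endpoint

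*Protocol article*

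**What the plan says.** All of the following is in the Data analysis section of the protocol article unless another section is named.

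- Estimator: "Time to first episode of decompensation and time to death (cause-specific and all-cause) will be assessed using Kaplan-Meier survival curves".
- Comparison of arms: "The curves will be compared with the log-rank test statistic", and "Cox proportional hazards modeling will be used to calculate HRs, after testing the proportional hazards assumption".
- Time at risk: "Patients will contribute person-time from the date of recruitment until the earliest of end of follow-up (12 months) or death".
- Competing risks, in the same paragraph: the events coded separately are "time to first readmission with a cirrhosis-related episode, death resulting from cirrhosis, or death resulting from other causes". First decompensation is not one of them.
- Mortality, from the section on power and sample size: "a 6-month mortality rate between 10% and 15% among the study cohort is predicted". That section derives this from a median survival of 2 years.

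The section on hospitalization and mortality says that the date, type and severity of decompensation events after enrollment will be collected, together with the hospital admissions. No section gives an expected decompensation rate. None says how first decompensation relates to first cirrhosis-related readmission.

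**The concern.** Kaplan-Meier treats a censored patient as someone who could still have the event later, at the same rate as those who remain under observation. A patient who has died cannot decompensate. If person-time for this endpoint simply stops at death, one minus Kaplan-Meier estimates the proportion who would decompensate in a population where nobody dies. That exceeds the proportion of each arm that actually decompensates within 12 months.

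Mortality in this cohort is high by the protocol's own prediction, and longer survival is a hypothesised benefit of the intervention (H8). If the intervention changed mortality, the two Kaplan-Meier curves would not show the true difference between arms in patients affected.

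The authors clearly accept the principle, because they plan a competing-risks analysis in the same paragraph. However, its non-fatal event is readmission. A decompensation managed without admission is an event for the Kaplan-Meier curve and is not one for the competing-risks analysis.

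**Working it through.** **Inputs**

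- From the protocol article: 6-month mortality 10% to 15%; median survival 2 years; 12 months of follow-up; at least 106 participants, so about 53 per arm.
- Assumed, because the document does not give them: the decompensation hazard h, and the share s of the death hazard that acts before any decompensation. Hazards are taken as constant and independent. First episode means first after recruitment, where person-time starts.

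**Step 1. The protocol's mortality figure.** A 2-year median gives a hazard of ln(2)/2 = 0.347 per year and 6-month mortality of 1 − exp(−0.347 × 0.5) = 15.9%. That is just above the top of the stated 10% to 15%, so the stated range is used.

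**Step 2. Death hazards.** d = −2 × ln(1 − 6-month mortality).

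- 10%: d = −2 × ln(0.90) = 0.211 per year, or 1 − 0.90² = 19.0% dead at 12 months.
- 15%: d = −2 × ln(0.85) = 0.325 per year, or 1 − 0.85² = 27.75% dead at 12 months.

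**Step 3. The two quantities at 12 months.** With m = s × d:

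- One minus Kaplan-Meier = 1 − exp(−h).
- Cumulative incidence = h/(h + m) × (1 − exp(−(h + m))).

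Worked case, h = 1.0 per year and s = 100%: one minus Kaplan-Meier = 1 − exp(−1) = 63.2%. At m = 0.211 the cumulative incidence is (1/1.211) × (1 − exp(−1.211)) = 58.0%. At m = 0.325 it is (1/1.325) × (1 − exp(−1.325)) = 55.4%. The overstatement is 5.2 to 7.8 points.

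**Step 4. Range over the unknowns.** Overstatement in percentage points, for 6-month mortality 10% / 15%:

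| One minus Kaplan-Meier at 12 months | s = 100% | s = 50% | s = 25% | s = 10% |
|---|---|---|---|---|
| 10% (h = 0.105) | 1.0 / 1.4 | 0.5 / 0.8 | 0.3 / 0.4 | 0.1 / 0.2 |
| 20% (h = 0.223) | 1.9 / 2.8 | 1.0 / 1.5 | 0.5 / 0.8 | 0.2 / 0.3 |
| 39.3% (h = 0.5) | 3.6 / 5.3 | 1.8 / 2.8 | 0.9 / 1.4 | 0.4 / 0.6 |
| 63.2% (h = 1.0) | 5.2 / 7.8 | 2.7 / 4.1 | 1.4 / 2.1 | 0.5 / 0.9 |
| 77.7% (h = 1.5) | 5.8 / 8.8 | 3.0 / 4.6 | 1.5 / 2.3 | 0.6 / 1.0 |

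**Step 5. Scale against sampling error.** With 53 per arm and a proportion near 55% to 58%, the standard error is about √(0.554 × 0.446/53) = 6.8 points. The overstatement at h = 1.0 and s = 100% is therefore about 0.8 to 1.1 standard errors of one arm's estimate.

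**Step 6. Effect on the contrast between arms.** Suppose h = 1.0 in both arms and the intervention halves the death hazard from 0.325 to 0.1625, with every death competing. One minus Kaplan-Meier is 63.2% in both arms. The proportions that actually decompensate are (1/1.1625) × (1 − exp(−1.1625)) = 59.1% with the intervention and 55.4% with usual care. The curves hide a difference of 3.7 points. The standard error of that difference is √(0.591 × 0.409/53 + 0.554 × 0.446/53) = 9.6 points, so it is about 0.4 standard errors.

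**The case against.** The case on the other side is substantial.

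- **The planned test and effect measure are sound.** The log-rank test and Cox hazard ratio with deaths censored compare cause-specific hazards, which is legitimate. The error lies only in absolute percentages read off the curves, and the protocol does not expressly commit to reporting a 12-month percentage from them. This stands, and it limits the point to the curves.
- **Competing risks are already planned for a close neighbour.** Decompensation dates are collected with the hospital admissions, so first decompensation and first cirrhosis-related readmission will overlap heavily. This stands in part: the omission is narrow, but no section equates the two events.
- **The endpoint is minor.** It is in none of H1 to H8 and is not listed in Table 3. This stands.
- **An article condenses a fuller plan.** This does not dispose of the point. The estimator, the end of person-time and the competing-risks event set are all stated here.

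Three stronger readings are tempting and are not supported.

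- A reader might quote a fixed bias of several points. Every such figure needs an assumed decompensation rate and an assumed share of deaths that come first. Deaths after a decompensation do not compete.
- A reader might take "dropouts due to death are informatively censored" as an admission about the Kaplan-Meier analysis. That sentence concerns imputation of missing survey responses.
- A reader might extend the criticism to cause-specific death, arguing that the readmission analysis misses deaths after a readmission. At 12 months the Kaplan-Meier error for that endpoint is small (at most 0.25 standard errors under the assumptions tried). The protocol also does not say that cause-specific mortality will be taken from the readmission analysis.

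**Conclusion.** The point holds in a limited form. As written, deaths before decompensation are in effect censored, and one minus Kaplan-Meier overstates the proportion of each arm that decompensates by 12 months. The direction is certain whenever any death comes first. The size is not fixed by the document. At the stated mortality it is under 1 point if only about a tenth of the death hazard acts before decompensation. It is about 1.0 to 1.4 points if 12-month incidence is near 10% and every death competes. It is 5.2 to 7.8 points at an assumed hazard of 1.0 per year with every death competing. The wider set of assumptions, including the 2-year median taken at face value, spans about 0.1 to 9.4 points.

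All of this rests on constant, independent hazards. It affects the absolute incidence for a non-primary endpoint. The planned hypothesis tests and hazard ratios are not affected.

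**What to change.** In the Data analysis section, add time to first decompensation to the competing-risks analysis. Report the Aalen-Johansen cumulative incidence by arm, with death before decompensation as the competing event, in place of one minus Kaplan-Meier. Keep the log-rank test and Cox model, and label them as comparisons of cause-specific hazards. Keep the readmission analysis for readmission. If the two events are meant to be the same, say so.

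The cost is a few lines of text and a little more analysis. The dates and causes needed are already being collected, and the change is still possible with recruitment complete. The planned software may need a supplementary package. The reported 12-month percentages will be slightly lower than those read from Kaplan-Meier curves.
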